### Evaluation procedures, data sources, and variable abstraction

Evaluation procedures are limited to review of medical records that will already be in existence. The evaluation will include participants who received treatment for OUD between 6/1/2022 and 1/1/2024 and a random sample of patients without OUD within the same date range. Follow up information will be included on all participants up until 1/1/2025.

Data will be collected through retrospective chart review of the ICC’s electronic medical record. Corresponding to the listed date ranges, these data will be measured at six months before implementation of MOUD 2.0 and six months after implementation. Data will then be de-identified and sent to team members for analysis.

Demographics and medical history will have already been included in the electronic medical record from the standard intake forms used to begin patient encounters. Variables to be abstracted from the medical record include:

Demographic information: age, sex, racial self-identification.Adherence to MOUD (categorical, based on positive buprenorphine toxicology or concurrent negative opioid and buprenorphine toxicology) at collection time point.Use of opioids during treatment periods.Months in MOUD program, up to 1 year.Month/year of MOUD visits.Month/year of LAIB injection.Results of urine drug screens while in program.Treatment Effectiveness Assessment Score (21).Results of HIV/HCV screening labs while in program.Dates, dosage, and quantity of buprenorphine prescriptions.

Adherence is difficult to determine from self-report in patients with OUD due to factors like diversion, stigma, and bias (26, 27). Previously published non-LAIB algorithms did not incorporate objective measures besides self-report. To improve accuracy in treatment, adherence will be determined based on toxicology as described in the algorithm.

The approach to urine drug screening was non-standard in the months prior to implementation and continues to reflect the harm reduction approach to treatment. Therefore, adherence will be operationalized as having a minimum of 3 buprenorphine- and norbuprenorphine-positive (“appropriate”) drug screens over a 6-month period regardless of substance use. Each screen should be at least 2 weeks apart within this time period. In each phase of the evaluation, participants will be dichotomized into “adherent” vs “non-adherent” using the above definition.

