## Methods

### Study objectives

The objective of this implementation evaluation is to assess whether the MOUD 2.0 algorithm improves treatment adherence and retention in the treatment program at the clinic-wide level, compared to these outcomes before implementation. The primary outcome measures are quantified adherence to MOUD and time length of retention in the treatment program.

Adherence will be operationalized as having a minimum of 3 buprenorphine appropriate drug screens (resulting positive for buprenorphine and norbuprenorphine) over a 6-month period regardless of substance use. Retention in treatment will be measured as the proportion of participants with at least 180 days of continuous pharmacotherapy with a medication prescribed for OUD, with no gaps greater than seven days (22). These outcome measures will show whether retention rates increase along with adherence, or whether the implementation favors one outcome measure over the other. The two measures are not mutually exclusive. In the context of an implementation evaluation, adherence could theoretically be more indicative of clinical response to the algorithm, whereas retention could characterize patient buy-in of the implementation. Secondary outcomes will include the percentage of patients starting LAIB for the first time, illicit use of substances per self-report and toxicology, and results of infectious disease while in the program.

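### As listed, month-level LAIB injection and visit records cannot decide the seven-day gap rule for retention during treatment periods on LAIB

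*Protocol article*

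**What the plan says.** Study objectives in the protocol article names two primary outcomes: "The primary outcome measures are quantified adherence to MOUD and time length of retention in the treatment program". A participant counts as retained on reaching "at least 180 days of continuous pharmacotherapy with a medication prescribed for OUD, with no gaps greater than seven days"; the share who do so is the retention measure. Data analysis adds unadjusted six-month retention curves before and after implementation.

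The section on evaluation procedures, data sources and variable abstraction lists the chart items. Four bear on retention:

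- "Month/year of LAIB injection"
- "Month/year of MOUD visits"
- "Months in MOUD program, up to 1 year"
- "Dates, dosage, and quantity of buprenorphine prescriptions"

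Only the last is listed with dates. The same section says that the abstracted data are de-identified and then passed to the analysts. No retention status judged on site appears in the list.

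**The concern.** The outcome is defined in days, while the injection, visit and programme-time fields are fixed in months. The article does not leave resolution open: it states month and year for two items and dates for another.

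Sublingual treatment can be followed through dated prescriptions with quantities. For LAIB, the field that records administration is the coarse one. Table 1 offers LAIB in three of its five status categories and, in two of them, makes LAIB or referral the end of a time-limited pathway. First-time LAIB starts are a secondary outcome. If LAIB use rises after implementation, a larger share of post-implementation treatment time rests on month-level data. The before-and-after retention comparison would then mix any effect of the algorithm with a change in measurement precision.

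**Working it through.** There is no stated figure to reproduce. The check asks whether month-level records can decide the rule.

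**Inputs.** The permitted gap is 7 days and the required duration 180 days (Study objectives). Injection resolution is month and year (variable list). Implementation was in January 2023, so 2023 month lengths are used. The article gives no days covered per injection; I assume a range of 26 to 35 days.

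**Step 1: range of intervals.** For injections on day a of March and day b of April, the interval is 31 − a + b days.
- Minimum (31 March, 1 April): 31 − 31 + 1 = 1 day.
- Maximum (1 March, 30 April): 31 − 1 + 30 = 60 days.
- For January–February and February–March the maximum is 58 days.

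**Step 2: ambiguity for one pair of months.** The uncovered gap is the interval minus the days covered. With 28 days assumed, the rule is broken when the interval exceeds 28 + 7 = 35 days, that is, when b − a is at least 5. For each a from 1 to 25 there are 26 − a such values of b. The sum is 25 + 24 + … + 1 = 325. Of 31 × 30 = 930 pairs, 325/930 = 34.9%.

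**Step 3: sensitivity to assumed cover.** Across the five consecutive-month pairs from January–February to May–June 2023:

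| Assumed days covered | Share of possible date pairs with gap over 7 days |
|---|---|
| 26 | 39.4% |
| 28 | 33.7% |
| 30 | 28.5% |
| 31 | 26.0% |
| 35 | 17.3% |

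**Step 4: identical records, opposite outcomes.** Take one injection in each month from January to July 2023, with 28 days covered.
- All on the 15th: the longest interval is 31 days, so the largest gap is 31 − 28 = 3 days. The rule is met.
- The same, except that February's is on the 2nd and March's on the 28th: that interval is 54 days and the gap is 54 − 28 = 26 days. The rule is broken.

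With 30 days covered the largest gaps are 1 and 24 days, and the conclusions are unchanged. The month-and-year entries of the two patients are the same.

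**Step 5: a skipped month.** A missing month does not prove a gap. With one calendar month skipped, the shortest interval is 29 to 32 days, depending on the months. At 28 days covered that leaves 1 to 4 days, within the allowance.

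**The case against.** The strongest reply is that the list also contains dated buprenorphine prescriptions and does not limit them to sublingual forms. LAIB is buprenorphine, and retention is worded around prescribed medication, so those records might supply the dates. This stands in part, and it is why a reader should not infer that retention is impossible to compute for LAIB patients. It does not close the gap: injections are listed separately and more coarsely, nothing says the prescription item includes LAIB, and an order date does not show when an injection was given.

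A second reply is that day-level derivation could take place during chart review, with month and year only the resolution sent to analysts. The text neither says this nor rules it out, and the list has no retention variable derived that way.

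Other stronger readings are tempting but unsupported:

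- **Bias towards the post-implementation period.** Counting consecutive months as continuous would hide gaps, but counting a skipped month as a gap would create false ones (Step 5). The article specifies neither convention.
- **A problem for everyone the algorithm affects.** The algorithm also changes sublingual dosing, behavioural health follow-up, visit intervals and referral. Only LAIB treatment periods are at issue.
- **Adherence is also underivable.** Screen results are listed without a date, but the same section requires that "Each screen should be at least 2 weeks apart within this time period". Abstractors must therefore consult screen dates, and the missing word is a detail for the abstraction form.

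The article also presents the retention curves as a general impression, and its named test, McNemar's, concerns adherence. That limits the consequence, but retention remains a stated primary outcome.

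**Conclusion.** The point holds for treatment periods on LAIB. The listed month-level fields cannot determine whether the retention definition is met, because intervals of 1 to about 60 days share the same record. The 17% to 39% range rests on an assumed 35 to 26 days of cover and weights every date pair equally, including implausibly close ones. A reader might take it as an expected error rate. It is not one, since it ignores any injection schedule and the number of patients on LAIB is not given. The effect on estimated retention therefore cannot be quantified from the article.

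If LAIB use rises after implementation, precision falls in the post-implementation period. The net direction of bias is unknown. This should be corrected before the data are abstracted or, if abstraction is complete, before the file is analysed.

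**What to change.** Replace the month-and-year entries for LAIB injections and MOUD visits with exact dates. Convert these on site to day offsets from the implementation date before de-identification. Derive the seven-day gap from the offsets, using a days-covered rule per injection that is stated in advance and taken from the product used. This is an analysis convention and implies nothing about how often injections should be given. State also whether the dated prescription item includes LAIB.

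The cost is a change to the abstraction form and a little extra data handling on site. The source is the same chart, no patient contact is needed, and calendar dates stay out of the analysis file. No sample size or power figure changes.

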### MOUD 2.0 algorithm

The MOUD 2.0 algorithm was implemented at the clinic-wide level in January 2023. Staff at the ICC, Pathways to Housing PA, and PHHS developed the algorithm for use at follow-up visits for OUD after the initial diagnosis visit (see **Table 1** and below **Figure 1**). The algorithm has 4-, 8-, and 12-week decision points to guide treatment for patients with varying responses to sublingual and injectable buprenorphine.

**Table 1 T1:** MOUD 2.0 status and algorithm responses.

Status	Symptoms	Opioid Use	Opioid level	BUP adherence	BUP level	Plan	Visit interval
Full response	Improved	None	Negative	Full	Appropriate	Continue current dose	2 weeks in-person alt 2 week TH option OR 4 weeks in-person
Partial response with BUP	Improved	Some	Positive	Partial	Appropriate	Consider: Increase dose Regular BH f/u LAIB	2 weeks in-person alt 2 week TH option
Partial response without BUP	Improved	Some	Positive	Partial	Negative OR Adulterated OR Late	Review dosing method Consider: Increase dose Regular BH f/u LAIB	2 weeks in-person for up to 12 weeks LAIB or refer at week 12
Minimal or nonresponse without BUP	No improvement	Some	Positive	Partial	Negative OR Adulterated OR Late	Review dosing method Consider: Increase dose Regular BH f/u LAIB	2 weeks in-person for up to 8 weeks LAIB or refer at week 8
Reconsider diagnosis of OUD	Any	Any	Negative	Any	Negative OR Adulterated OR Late	Review hx/reconsider diagnosis of OUD	2 weeks in person Discharge or refer at 4 weeks

“Appropriate” indicates buprenorphine and norbuprenorphine detected in urine without contaminants.

*BUP* buprenorphine, *BH f/u* behavioral health follow up, *LAIB* long-acting injectable buprenorphine, *OUD* opioid use disorder, *alt TH* alternating telehealth.

**Figure 1 f1:**
[figure not shown]
Clinical decision algorithm for treating opioid use disorder with sublingual and injectable buprenorphine.

Patients are clinically categorized as “full response,” “partial response with buprenorphine,” “partial response without buprenorphine,” “minimal or nonresponsive without buprenorphine,” and “reconsider diagnosis of OUD.” Note that “full” or “partial response” in the algorithm refers not to adherence or non-adherent outcomes but are clinical categories of physiological response informing further treatment decisions. Physiological response is important *within* the algorithm but is not an outcome measure for successful algorithm implementation.

Depending on the response, the algorithm recommends a plan and follow-up interval. Categories are based on subjective improvement of OUD symptoms in response to buprenorphine, in combination with objective measures of MOUD adherence. Symptoms include cravings, withdrawals, and interference with other activities and functioning with reference to DSM-5 diagnostic criteria for OUD, and are subjectively reported by the patient as improved, the same, or worse compared to the previous visit.

Because a major goal of MOUD 2.0 is increasing buprenorphine adherence, toxicology is included as a clinical data point to guide decision-making (28). Patients subjectively report non-prescribed opioid use, which is confirmed by urine or saliva drug screen including fentanyl and other opioids. Urine testing for appropriate levels of buprenorphine and metabolites confirms buprenorphine adherence. The combination of subjective patient report, urine opioid screen, and urine buprenorphine testing results in the patient’s status that the algorithm assigns (see **Table 1**).

For example, “full response” patients report improved symptoms, demonstrate appropriate qualitative levels of buprenorphine and its metabolite norbuprenorphine, and show no evidence of opioid use on urine screen. Improved symptoms include findings such as fewer cravings, better functioning in everyday activities, and less time spent for obtaining opioids, etc. (19). These patients continue their regimen of buprenorphine and clinic visits every 2-4 weeks, at shared discretion. Buprenorphine dose will remain unchanged as their current dose and delivery route of buprenorphine appear to be working well.

Patients with partial responses may have some improvement of OUD symptoms but still demonstrate some use of opioids by self-report or urine screen. They are either not being sufficiently treated with buprenorphine or are non-adherent to medication. If urine shows buprenorphine and norbuprenorphine, the dose of sublingual buprenorphine may be too low, or the patient would benefit from LAIB. If urine is negative for buprenorphine and the patient demonstrates opioid use, treatment should progress with redosing or LAIB within a 12-week timeline. This timeline ensures the patient benefits from treatment while limiting medication diversion and other negative social effects, as further MOUD treatment for non-adherent patients in primary care may cause net harm. Patients with little or no response to treatment, i.e. without OUD symptom improvement and without adherence to buprenorphine treatment, are likewise accounted for.

LAIB provides a definitive treatment for suitable patients within the various visit timelines, and it can also be used earlier in treatment for motivated patients. Closer follow-up benefits patients who need dose adjustments. The clinician using the algorithm adjusts buprenorphine dosing, recommends injectable buprenorphine, or refers the patient to another program as indicated.

### Algorithm development, staffing, and funding in a low-barrier setting

The ICC, the setting for the development of the algorithm, provides medical, behavioral health, substance use treatment, and housing services. Since 2016, the clinic’s services have included low-barrier, primary care-based MOUD. The low-barrier approach was first described with methadone maintenance therapy (29) and has been extended to buprenorphine treatment (30). This approach includes same-day treatment entry, harm reduction, flexibility in appointments and prescribing, and combining services in one location.

The ICC participates in the Pathways housing-first model, which offers immediate access to one-bedroom scattered-site apartments with intensive support services for people with experiences of chronic homelessness. All participants have a diagnosis of a serious mental illness or substance use disorder. Many participants were previously living unsheltered in the Kensington neighborhood of Philadelphia, a neighborhood often called the “epicenter of the opioid crisis,” with high levels of OUD, homelessness, food insecurity, and early mortality (31–33). The ICC continued increasing the number of people treated for OUD and modified its services throughout the COVID pandemic. As multiple other low-barrier MOUD clinics have reported, the ICC MOUD program made several intentional adjustments to MOUD care delivery to facilitate access despite disruptions. Such adjustments included: 1. extended visit intervals of up to 2 weeks during the initiation and stabilization phase of treatment with telehealth options, and, 2. a goal of monthly urine drug screening for all patients, but tolerating longer intervals without penalty.

This approach was successful in preserving access and retention in services from March 2020–March 2022. However, as an unintended consequence, the clinical team expressed increasing concerns regarding non-adherence to buprenorphine and lack of consistency in programmatic response, calling into question the program’s overall effectiveness. These concerns and the recent introduction of LAIB to clinical practice necessitated the algorithm’s development and an implementation evaluation to assess the algorithm’s effectiveness. Following the program’s philosophy of participation, the algorithm and implementation process were refined over a series of meetings with the medical team, separate meetings with the Center of Excellence care management team, meetings with Pathways leadership and Project HOME leadership, and focus groups with current program patients.

The ICC partners with several other organizations to receive funding from the Pennsylvania Department of Human Services as an OUD treatment Center of Excellence. The Center of Excellence program provides funding for care managers at its partner sites. While the ICC’s operations are funded by the Center of Excellence program, this evaluation does not receive additional funding for its development and execution.

### Data analysis

Baseline and demographic characteristics will be summarized with descriptive statistics such as means and standard deviations for continuous variables such as age and percentages for categorical variables such as race.

To accommodate the need for OUD treatment centers to have fair and ethical treatment of patients at the clinic-wide level, we will use patients as their own controls and assess six-month adherence before and after program implementation. The evaluation will follow the same patients, either adherent or non-adherent at six months before algorithm implementation, by chart review to see if they crossed over to the opposite outcome six months after implementation. We will present adherence at endpoints six months prior to and six months after MOUD 2.0 implementation as proportions. We will qualitatively compare the proportion of adherence six months prior, i.e. adherence in 2022, to the proportion six months after. Then, a chi-squared test will compare discordant pairs, i.e. patients who became newly adherent after MOUD 2.0 and patients who became newly non-adherent.

Because we are treating adherence as a binary outcome, we will use McNemar’s test to determine differences in adherence before and after implementation, with each individual patient before and after implementation as a paired sample. The Chi-squared test statistic for McNemar’s test takes the form:

$$\chi^{2}=\frac{{\left(b-c\right)}^{2}}{b+c}$$

where χ^2^ follows the chi-squared distribution with 1 degree of freedom, *b* represents the patients who were adherent before and were not adherent after, and *c* represents the patients who were not adherent before and were adherent after.

Finally, we will present unadjusted six-month survival curves for retention before and after implementation. While comparing unadjusted survival curves before and after MOUD program implementation has potential for survival bias (i.e., individuals need to “survive” to program implementation in order to be considered for post-implementation calculations), this comparison is given to provide a general sense of how MOUD 2.0 might affect the clinic overall and not to predict explicit dropout rates. If there is a significant number of patients not retained, descriptive statistics for this group will be reported to characterize factors associated with dropout. Secondary outcomes such as receipt of LAIB and use of opioids and of other substances during the evaluation periods will be analyzed with linear regression models for descriptive purposes. These primary and secondary outcomes may also be used for a future stepped wedge analysis in other clinics that could use the algorithm prospectively.

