### Setting and population

Given the clinic’s size and an accrual time of 2 years including before and after algorithm implementation, we anticipate approximately 100 participants for this evaluation. Participants will be individuals age 18 or older with current or past experience of homelessness and a diagnosis of OUD. All participants are patients at the ICC. Demographic information will be reported. The sample for comparing adherence will be restricted to participants already enrolled in the ICC for management of OUD prior to the algorithm implementation, measuring adherence at 6 months prior to implementation and 6 months after. Survival curves will be drawn from all aggregated patients in MOUD programs at 6 months pre-implementation to implementation or dropout, and from 6-12 months post-implementation or dropout.

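### Retention is a primary outcome, but its only described before/after comparison is a pair of calendar-clock curves whose conceded survival bias is left uncorrected

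*Protocol article*

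**What the plan says.** Study objectives states: "The primary outcome measures are quantified adherence to MOUD and time length of retention in the treatment program". The same section gives a working definition: "Retention in treatment will be measured as the proportion of participants with at least 180 days of continuous pharmacotherapy" with a drug prescribed for OUD, "with no gaps greater than seven days". Sample size and power again counts six-month survival in the program among the primary outcomes and refers to a proportional-hazards formula.

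The comparison is in Data analysis: "Finally, we will present unadjusted six-month survival curves for retention before and after implementation". The clock is in Setting and population: "Survival curves will be drawn from all aggregated patients in MOUD programs at 6 months pre-implementation to implementation or dropout", with the after curve taken from 6-12 months post-implementation. Data analysis concedes the weakness ("While comparing unadjusted survival curves before and after MOUD program implementation has potential for survival bias") and gives the mechanism, that "individuals need to “survive” to program implementation in order to be considered for post-implementation calculations", and then says the comparison is meant as an overall impression of the clinic and not as a prediction of dropout rates. No correction follows.

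The abstraction list in Evaluation procedures includes "Dates, dosage, and quantity of buprenorphine prescriptions", the month and year of visits, and months in the program capped at one year. It lists no episode start date.

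**The concern.** Both curves start at a calendar date, so each mixes patients in their first weeks of treatment with patients who have been in the program for years. If dropout risk falls with tenure, a group that has already stayed longer will show better six-month retention whatever the clinic does. The after curve can therefore look better than the before curve with no change in anyone's risk of leaving.

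Naming the bias does not remove it. The objective is to learn whether retention improves, and readers will take this pair of curves as the answer. A second, quieter problem is that a curve dominated by long-tenured patients says little about retention from the start of treatment.

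**Working it through.** **Plan's own figure.** The article gives no figure for the bias and no dropout rate. Its sample size of 86 has no stated inputs, so it can be neither confirmed nor refuted. Nothing below depends on it.

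**Inputs from the article.** MOUD services since 2016 (Algorithm development); implementation in January 2023; inclusion from 6/1/2022; about 100 patients.

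**Assumptions not in the article.** No algorithm effect. Uniform intake for 77 months before the first window (January 2016 to June 2022). Half of starters leave at hazard h₁ and half at h₂ per month.

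**Closed cohort.** At window opening, group i has weight Aᵢ = 0.5(1 − e^(−77hᵢ))/hᵢ. The number still present t months later is R(t) = Σ Aᵢe^(−hᵢt). The before curve ends at R(6)/R(0). The after curve ends at R(12)/R(6) if it starts at implementation, or at R(18)/R(12) if it covers 6 to 12 months post-implementation.

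- h = 0.15 and 0.02: A = 3.333 and 19.640; R(0), R(6), R(12), R(18) = 22.974, 18.775, 16.001, 13.927.
- h = 0.08 and 0.03: A = 6.237 and 15.012; R = 21.249, 16.399, 12.862, 10.226.

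| Hazards | Before | After, 0-6 months | After, 6-12 months | Spurious gain (points) |
|---|---|---|---|---|
| 0.15 / 0.02 | 81.7% | 85.2% | 87.0% | 3.5 to 5.3 |
| 0.08 / 0.03 | 77.2% | 78.4% | 79.5% | 1.3 to 2.3 |

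**Other dropout shapes.** A simulation with Weibull dropout (shape 0.5, 0.7 or 1.0; true six-month retention from start 40%, 50% or 60%; intake uniform or growing 2% a month) gave these closed-cohort results:

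- Falling hazard, after window starting at implementation: gain of about 2 to 7 points, for example 73.9% to 79.5%.
- Falling hazard, after window at 6-12 months: about 3 to 10 points, at most 70.8% to 81.2%.
- Constant hazard (shape 1.0): essentially 0.

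**Open cohort.** If each curve takes whoever is in the program when its window opens and intake is steady, the first pair of hazards gives 81.7% before and 81.9% after: extending intake from 77 to 83 months barely changes the tenure mix. The levels are still not those of new starters. Retention from the start of treatment under the same hazards is 0.5e^(−0.9) + 0.5e^(−0.12) = 64.7%, which is 17 points lower. In the Weibull runs with falling hazard the excess was about 15 to 34 points.

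**Does the correction work?** On time since MOUD start, with delayed entry at window opening and censoring at its end, the simulated six-month estimate fell within about 1 point of the truth in both periods in every scenario. With an assumed post-implementation hazard ratio of 0.7 and true values of 50% and 0.5^0.7 = 61.6%, it returned 49.7-50.3% and 61.5-61.6%.

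**What it costs in precision.** Scaled to 100 patients, about 27 to 56 contribute per period, with about 6 to 22 dropouts and a standard error of about 8 to 12 points. If only starts since 1 June 2022 are used, about 18 to 36 contribute before implementation and the standard error there is about 13 to 16 points.

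**The case against.** The best defence is that the authors name this mechanism, attach no test or hazard ratio to the curves, and offer them only as a broad picture. The clinic is described as serving a steady population, new patients keep enrolling, and only the adherence sample is limited to those already enrolled. Under that open reading the before/after difference is near 0. This stands as a limit on size. It does not supply a valid comparison for an outcome that the objective and the sample-size section both treat as primary, and the article does not settle which reading applies.

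Three stronger readings are tempting and are not supported:

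- **A gain of 9 to 16 points.** With hazards 0.15 and 0.02, retention is 64.7% from start, 73.6% for those 6 months in and 80.4% for those 12 months in. That contrast uses new starters as the before group, but the planned before curve is itself a pooled cohort.
- **The after curve must look better.** This needs both a closed cohort and falling hazard.
- **Everything needed is already abstracted.** No start date is listed, tenure is capped at one year, and the article does not say whether prescriptions before 6/1/2022 are captured.

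It is also fair to object that the correction's standard error exceeds most of the bias it removes, and that a 0-6 month tenure curve leaves out patients already past six months, whereas the objective is clinic-wide. Both are reasons to keep the calendar curves alongside. How mid-window joiners are handled may be in the full protocol, and I make no finding of it.

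**Conclusion.** The point holds as a weakness in how a primary outcome is compared. The article does not hide it, and the retention result need not be wrong. With no algorithm effect, the spurious gain is roughly 1 to 10 points if the after curve follows survivors of the before cohort and dropout risk falls with tenure, and near 0 with constant hazard or an open cohort in a steady clinic. In the open case with falling hazard, both curves still overstate retention of new starters. The range depends on assumed hazards and intake. The direction depends only on risk falling with tenure and on the cohort being closed. The description of the curves as a general impression does not fit the rank given to retention elsewhere in the article.

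**What to change.** - **Setting and population; Data analysis.** Make the main retention comparison a left-truncated Kaplan-Meier curve on time since the start of the MOUD episode, with delayed entry at window opening and censoring at window end. Keep the calendar curves, labelled descriptive.
- **Evaluation procedures.** Add the episode start date or, at the least, identify episodes that began within 6 months before each window. Patients already beyond six months at opening add nothing to a 0-6 month curve, so the one-year cap on tenure is not itself an obstacle.
- **After window.** Reconcile 6-12 months post-implementation in Setting and population with six months after implementation in Evaluation procedures. The later start adds a further survival requirement.
- **New starters only.** Use at most as a supplementary display. To reach 180 days before implementation, a patient must have started by 5 July 2022 if implementation was on 1 January 2023, or by 4 August 2022 if it was on 31 January.

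The cost is one abstracted field and the loss of precision shown above. Delayed entry also assumes that entry time is unrelated to dropout risk given tenure, and it leaves calendar trends and other before/after confounding in place. The article should say so.
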